#### The control group

In the control group, patients will receive standard medical therapy based on current guidelines (20). The antithrombotic regimen will be aspirin 100 mg daily for the duration of follow-up and clopidogrel 75 mg daily for 90 days after enrollment, with continuation determined by the local investigator. For clopidogrel-resistant patients, the investigator may switch to ticagrelor. Lipid-lowering therapy with statins or PCSK9 inhibitors will achieve a low-density lipoprotein target of <1.8 mmol/L (70 mg/dL). Blood pressure will be maintained at <140/90 mmHg.

Timely and positive control of risk factors in both groups will include smoking cessation, a low-salt, low-fat diet, and appropriate exercise.

In the prospective cohort study, eligible patients will receive either SBA with standard medical therapy or standard medical therapy alone based on the decision of the patient or legal representative.

### Outcomes

The primary outcome is a composite of stroke (hemorrhagic and ischemic), or death within 30 days, or ischemic stroke in the culprit artery territory from 30 days to 1 year. Secondary outcomes will include stroke (hemorrhagic and ischemic) or death within 30 days, ischemic stroke in the culprit artery territory from 30 days to 1 year, restenosis of the culprit artery at 1 year defined as exceeding 50% of the stenosis degree or narrowing reaching or surpassing the stenosis degree at the time of the procedure, and neurological functional outcome at 90 days (assessed using the mRS score). Safety outcomes include intracranial hemorrhage within 30 days and endovascular complications. Follow-up will occur at 24 h, discharge, 30 days, 90 days, and 1 year after enrollment. All clinical outcomes including stroke and mRS will be evaluated by certified assessors who are blinded to allocation treatment.

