**Inclusion criteria**
1.age range of 30–80 years;
2.symptomatic ICAS (C4–C7 segments of ICA, M1 segment of the MCA, V4 segment of the VA, and BA) with 70–99% stenosis confirmed by DSA;
3.minor stroke (NIHSS score ≤ 5) within 1 week of onset or from symptom exacerbation (NIHSS score increased by ≥2 points) or intermediate- to high-risk TIA, defined as ABCD^2^ score ≥ 4 within 1 week of the last symptom episode;
4.diameter of the culprit artery ranging from 2.0 to 4.5 mm, and the length of the stenosis≤14 mm;
5.mRS ≤ 2 before endovascular treatment;
6.no large ischemic region found on CT or MRI (ASPECTS ≥ 6 or pc-ASPECTS ≥ 8);
7.written informed consent obtained from the patient or legally responsible person.

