### Treatment strategy

#### The SBA group

In the SBA group, patients will undergo SBA within 1 week of stroke or TIA onset on the basis of standard medical therapy (20). SBA aims to improve stenosis of the culprit artery by more than 20%.

The procedure involves the following steps: (1) Under general or local anesthesia, femoral artery access is obtained, and heparinization is performed (trans-radial access may be used for posterior circulation, aortic arch or abdominal aortic tortuosity); (2) A 6–8F guide catheter is selected per operator preference (an access catheter may be used if the anatomy is tortuous); (3) The diameter of the stenosis, diameter of the artery proximal and distal to the artery is measured; (4) An 0.014 microwire is passed through the lesion into the distal branch of the artery, with microcatheter assistance as needed; (5) The balloon with a diameter of 50–80% of the normal vascular diameter is advanced over the microwire to the lesion, and is slowly inflated (1 atm/min) for 30–120 s, then deflated. If no major dissection or rupture is observed, the balloon is withdrawn while the wire remains in place. Intraprocedural antiplatelet therapy (glycoprotein IIb/IIIa receptor antagonist) may be administered as needed; (6) Angiography is performed after balloon removal to assess the stenosis. If the stenosis is improved by >20% without major dissection, repeat angiography is done within 10–15 min. If the improvement is maintained, the procedure is complete; otherwise, up to 3 repeat dilatations may be performed.

Rescue stenting may be performed if the following occurs: (1) After SBA, residual stenosis remains>80% or forward flow is unstable with a modified Thrombolysis in Cerebral Infarction (mTICI) score < 2b; (2) local dissection causes unstable distal flow and mTICI < 2b.

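### The 1-year restenosis outcome is not limited to the SBA group, yet every control patient meets its 50% limb at enrolment and some SBA patients can meet it on the day of the procedure

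*Protocol article*

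**What the plan says.** The Outcomes section of the protocol article gives, among the secondary outcomes, "restenosis of the culprit artery at 1 year defined as exceeding 50% of the stenosis degree or narrowing reaching or surpassing the stenosis degree", and the sentence continues "at the time of the procedure, and neurological functional outcome at 90 days". Neither this section nor the Abstract limits restenosis to patients who had a procedure. The Data analysis section sends primary and secondary outcomes together to linear or Cox regression, adjusted for age, sex, NIHSS, pre-stroke mRS and presentation as TIA or stroke.

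Three other places bear on the definition:

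- **Entry (Table 1, inclusion criterion 2):** the culprit lesion must be present "with 70–99% stenosis confirmed by DSA". This applies to both groups.
- **Control treatment (The control group):** medical therapy and risk-factor control, with no dilatation.
- **Procedure (The SBA group):** "SBA aims to improve stenosis of the culprit artery by more than 20" percent. The completion rule reads "If the stenosis is improved by >20% without major dissection, repeat angiography is done within 10–15 min", then "If the improvement is maintained, the procedure is complete; otherwise, up to 3 repeat dilatations may be performed". One of the conditions that permits rescue stenting is "After SBA, residual stenosis remains>80" percent. The balloon is sized at 50–80% of the normal vessel diameter.

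**The concern.** Restenosis means loss of a lumen that had been regained. The printed definition does not require that anything was regained. Its 50% limb lies below the lowest stenosis at which a patient may enter, so an untouched control artery satisfies it unless the plaque regresses. The same limb can be satisfied by an SBA artery that the protocol regards as successfully treated, because the completion rule is set by the amount of improvement and not by the residual.

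If the groups are compared on this outcome, a large difference in favour of SBA could appear although no treated artery had narrowed again. The planned covariates cannot remove a difference that the definition creates. If only SBA patients are described, the rate still mixes arteries that were left above 50% with arteries that later narrowed.

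**Working it through.** The documents give no expected rate or power figure for restenosis, so there is none to reproduce. The stated total of 368 belongs to the primary outcome (15% vs 5%, 90% power, two-sided 0.05): (1.960 + 1.282)² × (0.15×0.85 + 0.05×0.95) / 0.10² gives 184 per group, 368 in total. Restenosis does not enter it.

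**Step 1. Controls, first limb.** The wording can be read in two ways.
- *More than 50% stenosis.* The lowest entry value is 70, and 70 > 50, so 100% of controls meet it at enrolment.
- *More than half of the patient's own stenosis degree.* The threshold runs from 70/2 = 35% to 99/2 = 49.5%. Again 100% of controls meet it at enrolment.

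**Step 2. Second limb.** Controls have no procedure, so there is no reference value. If baseline were substituted, an unchanged artery would count as an event. In SBA patients the reference is unclear:
- If it is the pre-procedure degree (70% or more), the limb adds nothing, because any such value already exceeds 50%.
- If it is the post-procedure residual, merely reaching that value counts, so an artery stable at 30% for a year would be called restenosed.

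**Step 3. SBA group, highest residual compatible with completion.** The article does not say whether the 20% is in percentage points or relative. Because the rule is *more than* 20%, each residual below is an upper bound that is not quite reached.

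| Entry stenosis | Points: entry − 20 | Relative: 0.8 × entry | Gain needed to reach 50% |
|---|---|---|---|
| 70% | 50% | 56% | 20 points |
| 80% | 60% | 64% | 30 points |
| 90% | 70% | 72% | 40 points |
| 99% | 79% | 79.2% | 49 points |

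Completion with a residual above 50% is possible for every entry value above 70% on the points reading, and for the whole range 70–99% on the relative reading. Example: 90% reduced to 65% is a gain of 25 points, or 25/90 = 28% relative. It meets the procedural aim on either reading, and 65 > 50 (also 65 > 45, half of 90).

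**Step 4. It need not happen.** A balloon of 50–80% of normal diameter, fully expanded and without recoil, leaves 100 − 80 = 20% to 100 − 50 = 50%. None of these values exceeds 50%.

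**Step 5. Illustration under assumptions.** The documents give no distribution of residual stenosis. Assume entry stenosis uniform on 70–99%, residual normal with SD 10 points, completion at a gain of more than 20 points, and the first limb read as more than 50% stenosis. The share of completed SBA patients already above 50% on the day of the procedure, and the gap from the 100% of controls above 50% at entry, are:

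| Assumed mean residual | SBA already >50% | Gap from controls |
|---|---|---|
| 30% | 2% | 98 points |
| 40% | 13% | 87 points |
| 50% | 42% | 58 points |
| 60% | 75% | 25 points |

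The gap exists before any artery has had time to narrow again.

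**The case against.** The strongest reply is that the outcome was meant for treated arteries only. The word itself presupposes a treated lesion, the second limb is tied to a procedure, and the Data analysis section names no restenosis comparison. On that reading the built-in group difference disappears. This is plausible, but the article does not settle it: the outcome is listed without restriction, and secondary outcomes are assigned to adjusted regression as a set. Even on the SBA-only reading, the mixing of residual stenosis with restenosis remains.

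A reader might also infer more than the text supports:

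- *That every completed SBA patient meets the definition on day 0.* Not so. The balloon sizing points to a nominal residual of 20–50%, and a gain of more than 20 points from 70% ends below 50%. The share is unknown; the 2% to 75% above depends wholly on the assumed mean residual.
- *That the 1-year control rate will be 100%.* The 100% is status at entry. Controls receive lipid lowering to below 1.8 mmol/L, and some lesions may regress to 50% or less.
- *That the trial's main result is at risk.* The primary outcome, safety outcomes and sample size do not use restenosis.

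That the article condenses a fuller protocol is not an answer here. The definition is printed, and the difficulty lies between it and the printed entry and completion rules.

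**Conclusion.** The definition is wrong as written for a two-group study and should be corrected, as a matter for one secondary outcome. It is certain from the entry criterion alone that all controls satisfy the 50% limb at enrolment, on either reading of the wording, and that the second limb has no meaning for them. It is also certain that some SBA patients can satisfy it on the day of the procedure, with residuals up to just under 79% (points) or 79.2% (relative) from a 99% lesion. How many will do so cannot be derived from the documents.

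A between-group comparison would therefore largely show that one group was dilated and the other was not, and would lean towards SBA by construction. This conclusion assumes only that the outcome is applied to both groups as listed. If it is applied to SBA patients alone, the remaining fault is that residual stenosis is counted as restenosis.

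**What to change.** 1. Do not test the present definition between groups.
2. Restrict restenosis to the SBA group and report it descriptively. Define it relative to the residual stenosis on the immediate post-procedure angiogram, with a loss threshold that the sponsor prespecifies. The documents give no basis for a particular value, and none is proposed here. The outcome definition and the completion criterion in The SBA group must be reconciled, including whether the 20% is absolute or relative.
3. If a between-group vessel outcome is wanted, compare core-laboratory percent stenosis of the culprit artery at 1 year, adjusted for baseline percent stenosis. Use the same imaging modality in both groups, and label it luminal stenosis or patency. It will still favour a dilated artery; the label makes clear that this is what it measures.

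The cost is mainly wording. Post-dilatation angiography, a 1-year vessel assessment and an imaging core laboratory are already part of the plan or required by the outcome. The binary between-group restenosis rate is lost. The text does not state the 1-year imaging modality; if it is not DSA, adjusting for a DSA baseline mixes modalities, and that should be acknowledged. Recruitment is planned to December 2026, with 40 patients enrolled at first submission of the article, and no treatment rule has to change.

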### Data management and quality control

All data will be recorded in the patient’s case report form. The independent Data Safety and Monitoring Committee (iDSMC) will check the data for safety reasons. The iDSMC reserves the right to terminate the study prematurely if unexpected high rates of complication or ICH rates in SBA group during the research. A central core laboratory for imaging is created to judge intracranial hemorrhage events (ECASS definition) and assess neuroimaging data. The protocol is designed by [name] and [name], and is discussed by the trial steering committee. The trial steering committee consists of external scientific advisors who will regularly monitor the research and data. The trial steering committee will organize teleconferencing or physical meetings to provide recommendations regarding the study.

### Sample size estimates

Based on previous studies, the 1-year incidence of the primary outcome is estimated to be 15% with medical therapy alone (10, 21). We hypothesize this would decrease to 5% with SBA combined with medical therapy (15). With 90% power and an alpha value of 0.05 (two-sided), the sample size required to test superiority is 368. Accounting for a 10% loss to follow-up and alpha spending for the interim analysis (O’Brien-Fleming), the total sample size is 416. Thus, 416 patients will be enrolled (208 per group).

### Data analysis

The baseline patient characteristics will be presented in both groups. Categorical variables will be expressed as frequencies and percentages. Chi-square tests will be used to compare differences between groups. Continuous variables will be presented as mean ± standard deviation or median and quartiles after testing for normality using the Kolmogorov–Smirnov test. The Student’s *t*-test or the Mann–Whitney U test will compare group differences based on normality. Missing data will be handled using multiple imputations.

Primary and secondary outcomes will be analyzed using linear or Cox regression, as appropriate, after adjusting for key prognostic factors (age, sex, baseline NIHSS score, and pre-stroke mRS score, and presention with TIA vs. stroke). Statistical analysis will be performed using SPSS 24.0, with two-sided *p* < 0.05 considered statistically significant.

The primary endpoint will further be stratified by age (≤65 vs. >65 years), gender (male vs. female), hypertension (yes vs. no), diabetes mellitus (yes vs. no), smoking (yes vs. no), baseline SBP (<140 vs. ≥140 mmHg), clinical presentation (TIA vs. stroke), mechanism of stroke (i.e., borderzone vs. perforator vs. embolic), lesion location (anterior circulation vs. posterior circulation), whether the patient is already on pre-stroke aspirin or DAPT.

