### Target population

A total of 416 patients from 20 hospitals in China will be enrolled and allocated to either the SBA group (*n* = 208) or the control group (*n* = 208) based on patient treatment preferences. These centers are chosen based on high-capacity centers with neurointervention and good cooperation experience. Eligible patients are adults aged 30–80 years with symptomatic ICAS (70–99% stenosis) resulting in minor stroke (NIHSS score ≤ 5) within 1 week of onset or from symptom exacerbation (NIHSS score increased by ≥2 points) or intermediate- to high-risk TIA, defined as ABCD2 score ≥ 4 within 1 week of the last symptom episode based on radiologic and clinical presentation. Eligible lesions include the intracranial segment of the internal carotid artery (segments C4–C7), the M1 segment of the middle cerebral artery, the V4 segment of the vertebral artery, and the basilar artery. The main exclusion criteria include allergy to contrast media non-atherosclerotic disease-related stenosis; penetrating branch lesion ipsilateral to the target lesion; presence of severe stenosis of the extracranial segment on the side of the target lesion; previous endovascular treatment of the ipsilateral vessel; presence of intracranial aneurysms, tumors, and vascular malformations; any form of ipsilateral intracranial hemorrhage within 3 months and contralateral intracranial hemorrhage within 2 weeks; presence of atrial fibrillation, severe heart dysfunction, liver or kidney dysfunction; patients with tumors and serious diseases whose expected survival time is ≤1 year; and others. The detailed inclusion/exclusion criteria are listed in Table 1. Before enrolling the first patient, all participating centers will receive standard training on the study protocol, inclusion/exclusion criteria, and other relevant details. Patients who meet the inclusion criteria and those who do not meet the exclusion criteria will be eligible to participate (Figure 1). All patients and their legal representatives will be required to sign informed consent.

**Table 1 tab1:** Inclusion and exclusion criteria.

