## Discussion

The BLAST study aims to evaluate the safety and effectiveness of early SBA combined with medical therapy compared to medical therapy alone in patients with minor stroke or TIA. The study population will comprise of patients with symptomatic ICAS (70–99% stenosis) resulting in minor stroke or TIA within 1 week after symptom onset.

No clinical trial has demonstrated the clear benefit of stenting over medical therapy alone for stroke caused by intracranial atherosclerosis. The SAMMPRIS trial, the first randomized controlled trial of stenting combined with medical therapy versus medical therapy for ICAS, was stopped early because of the higher 30-day stroke and death rate with stenting (14.7% vs. 5.8%, *p* = 0.002) (9). Similarly, the VISSIT study found higher 30-day recurrence after stenting (24.1% vs. 9.4%, *p* = 0.05) (10). More recently, the CASSISS study in China showed no difference in short or long-term recurrence between stenting plus medical therapy and medical therapy (8.0% vs. 7.2%, *p* = 0.82) (11). There are two potential explanations for these disparate results. First, a wide range of patients were enrolled. In the SAMMPRIS trial, patients had non-disabling stroke/TIA within 30 days (median, 7 days from onset to treatment) (9). The VISSIT study enrolled patients with TIA or stroke within 30 days of onset, with a median time of 9–15 days between onset and treatment (10). In the CASSISS study, patients experienced symptoms within 21 days (median, 35 days of treatment) (11). We contend that the benefit of an endovascular intervention decreases with longer onset-to-treatment time since prior studies have shown that carotid revascularization have the best outcomes within 2 weeks of symptoms (22).

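### Treatment is chosen by the patient, but the primary model adjusts for only five variables and leaves out recorded baseline factors, so the SBA estimate is open to avoidable residual confounding of unknown size and direction

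*Protocol article*

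**What the plan says.** The control group section says that "eligible patients will receive either SBA with standard medical therapy or standard medical therapy alone based on the decision of the patient or legal representative". The Target population section says the same of the 208 and 208 patients, who are allocated "based on patient treatment preferences".

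The Data analysis section analyses primary and secondary outcomes by linear or Cox regression, "after adjusting for key prognostic factors (age, sex, baseline NIHSS score, and pre-stroke mRS score, and presention with TIA vs. stroke"). This is a closed list of five. The article describes no weighting, matching or propensity score.

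The same section stratifies the primary endpoint by further baseline variables: "hypertension (yes vs. no), diabetes mellitus (yes vs. no), smoking (yes vs. no), baseline SBP (<140 vs. ≥140 mmHg"), "mechanism of stroke (i.e., borderzone vs. perforator vs. embolic), lesion location (anterior circulation vs. posterior circulation") and pre-stroke aspirin or DAPT. Table 1 requires the stenosis to be 70–99% on DSA and the qualifying event to fall within 1 week. Percent stenosis and time from the event must therefore be known at entry. Neither is in the model.

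The Discussion names the non-randomised design as the main limitation. It does not connect this to any analysis step.

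**The concern.** In a randomised trial a short list of prognostic covariates is enough, because allocation balances the rest on average. Here allocation is by preference, and covariate adjustment has to remove whatever differences preference creates. For that purpose the list should hold variables that may relate both to the choice of treatment and to recurrence. The five are instead described as key prognostic factors.

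Two of the five can do limited work. NIHSS is at most 5 for entry with stroke, and Table 1 caps mRS before endovascular treatment at 2. Lesion features, timing and vascular risk factors could plausibly differ between patients who accept an intracranial procedure and those who decline it, and they could plausibly affect recurrence. Using them as subgroup factors examines whether the effect varies; it does not adjust the main estimate.

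At stake is the study's only treatment comparison. Following the plan as written leaves measured potential confounders uncontrolled in it.

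**Working it through.** **1. The plan's own figure.** Inputs from Sample size estimates: 15% vs 5%, 90% power, two-sided 0.05. With unpooled variance, n per group = (1.960 + 1.282)² × (0.15×0.85 + 0.05×0.95) / 0.10² = 183.9, so 184 per group and 368 in total, as stated. Dividing by 0.90 for loss gives 409. The stated 416 leaves a further factor of about 1.017, which is plausible for the O'Brien-Fleming interim. The figure reproduces, but it makes no allowance for differences between self-selected groups.

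**2. Illustrative bias from one omitted factor.** The documents give no prevalences or risk ratios for the omitted variables, so these are assumptions. For a binary factor with risk ratio R and prevalence p_S in SBA and p_C in control, and no true SBA effect:

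apparent RR = [1 + (R − 1)p_S] / [1 + (R − 1)p_C]

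| R | 30% SBA vs 50% control | 50% SBA vs 30% control |
|---|---|---|
| 1.5 | 1.15/1.25 = 0.92 | 1.25/1.15 = 1.09 |
| 2 | 1.30/1.50 = 0.87 | 1.50/1.30 = 1.15 |
| 3 | 1.60/2.00 = 0.80 | 2.00/1.60 = 1.25 |

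**3. Effect on the test.** Analysable patients: 416 × 0.90 = 374, or 187 per group. Control risk 15%; SBA risk p = 0.15 × apparent RR. The chance of a false SBA win is Φ(z − 1.96), with z = (0.15 − p) / √{[0.15×0.85 + p(1 − p)]/187}.

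- R = 2, 30% vs 50%: p = 0.130, z = 0.020/0.0359 = 0.56, chance 8% (nominal 2.5%).
- R = 1.5, 30% vs 50%: chance 5%. R = 3: 13%.
- R = 2, reversed: p = 0.173, z = −0.61, chance of a false SBA win about 0.5%.
- R = 2, reversed, with the planned effect true: the SBA risk appears as 0.05 × 1.154 = 5.8% instead of 5%, and power falls from about 90% to about 84%.

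**4. Can the Cox model simply be enlarged?** Expected events under the planning rates: 374 × (0.15 + 0.05)/2 = 37.

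- Planned model: treatment + 5 covariates = 6 parameters; 37/6 = 6.2 events per parameter.
- Adding the subgroup variables (hypertension, diabetes, smoking, SBP, mechanism with 2 df, location, prior antiplatelet = 8 df): 14 parameters, 2.7 events each.
- Adding percent stenosis and time as well: 16 parameters, 2.3 events each.
- If there were no effect, events would be 374 × 0.15 = 56, and 56/16 = 3.5.

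On either assumption the outcome model cannot carry them all.

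**5. Can a propensity model carry them?** 5 + 10 = 15 parameters; 208/15 = 13.9 patients per treatment group per parameter. With 20 hospitals as 19 fixed terms the count becomes 34, and 208/34 = 6.1, no better than the existing Cox model. Centre therefore has to enter more sparingly.

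**The case against.** **Direction and certainty.** A reader might infer that the estimate will be confounded and will favour SBA. The documents do not support this. They say who decides, not what drives the decision. If higher-risk patients tend to choose SBA, the bias runs against it. This objection stands, which is why both directions are shown. Stacking several independent factors, all imbalanced by 20 points the same way, gives larger figures (for R = 2, two factors give 19% and three give 34%), but that is close to a worst case and nothing in the article points to it.

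**Restriction.** A reader might call adjustment the only protection. Eligibility also limits confounding: stenosis, vessel size, lesion length and timing are bounded, and penetrating-branch lesions and atrial fibrillation are excluded. This stands in part. A range of 70–99% stenosis or one week still leaves room for imbalance, and vascular risk factors are little restricted.

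**Timing.** The Discussion states "We contend that the benefit of an endovascular intervention decreases with longer onset-to-treatment time". It is tempting to read this as the authors naming time as a confounder. It is a claim about effect modification, argued across earlier trials with longer windows. Time belongs on the list as a plausible confounder, not because that sentence proves it.

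**Disclosure and the unseen SAP.** The article openly concedes that non-randomisation weakens its conclusion, and sensitivity analyses for confounding may sit in a SAP. Both are fair. But disclosure does not adjust the estimate, and the objection here is to a list the article itself fixes, not to missing detail.

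**Cost of the remedy.** Weighting loses precision, overlap weights move the target towards patients who might receive either treatment, and cluster-robust errors are fragile with 20 small centres. These points stand and shape the fix.

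**Conclusion.** The point holds as a fault in a stated rule. In a cohort allocated "based on the decision of the patient or legal representative", a closed five-variable list leaves recorded, plausibly confounding baseline variables uncontrolled in the primary comparison. The SBA estimate is liable to avoidable residual confounding.

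The illustration gives a sense of scale only. With R = 2 and a 20-point imbalance, the apparent risk ratio under no effect is 0.87 (about an 8% chance of a false SBA win against 2.5%) or 1.15, depending on which group carries the factor. These figures rest on assumed prevalences and risk ratios, a single binary factor not captured by the five covariates, a 15% control risk, 187 per group and a normal approximation. Neither the actual size nor the direction can be derived from the documents.

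**What to change.** Before any outcome analysis, pre-specify the following:

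- **Primary analysis:** a propensity-score analysis, for example overlap or inverse-probability weighting, with the target population stated. The score contains the five listed variables plus percent stenosis, lesion location, mechanism, time from qualifying event, hypertension, diabetes, smoking, baseline SBP and prior aspirin/DAPT.
- **Centre:** a random effect, or grouping or stratification, not 19 fixed terms.
- **Standard errors:** robust or bootstrap.
- **Balance:** judged by standardised differences rather than by chi-square and t-test p-values.
- **Sensitivity analyses:** keep the five-covariate Cox model, and add one for unmeasured confounding such as an E-value.

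Overlap weighting is one sound choice among several; the wider, justified confounder set matters more than the particular method.

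The cost is revised analysis wording, a little more analysis work, some loss of precision and possibly a different target population. The variables are already used as subgroup factors or needed to establish eligibility, so little or no new data collection should be required. The article reports 40 patients recruited at first submission and a recruitment target of December 2026, so the change can still be made in advance of the results.
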